### Interventions

The Baidu Jieduan granules are composed of 15 g of *Rheum palmatum L.* stem (*Dahuang*), 30 g of *Sargentodoxa cuneata (Oliv.) Rehd. et Wils.* (*Hongteng*), 30 g of *Taraxacum mongolicumHand.-Mazz.* (*Pugongying*), 45 g of *Raw Gypsum* (*Sheng Shigao*), 9 g of Herba Ephedra (*Mahuang*), 45 g of *Talcum* (*Huashi*), 12 g of *Amygdalus Communis Vas* (*Xingren*), 9 g of *Radix Glycyrrhizae (Gancao)*, 30 g of *Verbena officinalis L.* (*Mabiancao*), 30 g of *Polygonum cuspidatum* (*Huzhang*), 30 g of *Scutellariae Radix* (*Huangqin*) and 12 g of *Bombyx batryticatus* (Jiangchan), packaged in two bags. The Baidu Jieduan granules will be administered orally two times a day for 14 days. The Baidu Jieduan granules are manufactured by Beijing Tcmages Pharmaceutical Co., Ltd. (number: Jing 20180032).

The participants will be categorized into two groups receiving either standard Western medicine alone according to the *Protocol for Diagnosis and Treatment of Novel Coronavirus Pneumonia* (7th edition) or the combination of Baidu Jieduan granules two times a day for 14 days plus standard care. Routine care includes early fluid resuscitation, antimicrobial anticoagulants, nutritional support and other treatments. Other TCM therapies, including TCM injections and other oral herbal medicines, will be prohibited.

### Outcomes and measurements

The primary outcome will be the proportion of negative SARS-CoV-2 nucleic acid results on the 14th day. The secondary outcomes will be the time to symptom recovery, the proportion of cases with reversion on chest CT, the time to negative SARS-CoV-2 nucleic acid results and the proportion of participants regrouped as severe cases. Symptom recovery is defined as the complete disappearance of fever, fatigue and coughing symptoms.

Evaluation of the primary and secondary outcomes will occur at five points (before treatment and the 3rd, 5th, 7th and 14th days of hospitalization).

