**Methods/design:**

This multicentre, open-label, randomized controlled trial will be conducted in 300 patients with COVID-19. The patients will be randomly (1:1) divided into a treatment group and a control group. All patients will receive standard therapy at the same time. Patients in the experimental group will receive Baidu Jieduan granule treatment twice a day for 14 days. The outcomes will be assessed at baseline and at 3, 5, 7 and 14 days after treatment initiation. The primary outcome will be the rate of symptom (fever, fatigue and coughing) recovery. Adverse events (AEs) will be monitored throughout the trial.

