## Methods/design

### Study design and settings

The study is designed as a randomized, placebo-controlled, multicentre trial, which will be conducted at four medical centres selected by the expert committee: the Huangshi Hospital of Traditional Chinese Medicine; Tongji Hospital, Tongji Medical College, Huazhong University of Science and Technology; LaoHeKou Traditional Chinese Medicine Hospital; and Leishenshan Hospital of Wuhan. A total of 300 participants fulfilling the eligibility criteria will be randomized into two groups (Baidu Jieduan granule group and control group) at a ratio of 1:1. The study flowchart is illustrated in Fig. 1. The Standard Protocol Items Recommendations for Interventional Trials (SPIRIT) checklist is presented in Additional file 1.

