### Sample size

A similar clinical trial has been conducted using TCM to decrease the rate of symptoms (fever, fatigue and coughing) in patients with COVID-19 [14]. The rate of recovery of clinical symptoms was 91.2% in patients who received TCM treatment and 61.1% in patients who received conventional treatments. Considering 90% power with a significance level of 10%, as well as a rate of withdrawal and loss to follow-up of 10% [15], we plan to recruit at least 150 participants in each group to achieve sufficient precision in a subsequent full trial.

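### The article names two different primary outcomes, and its sample size rests only on the one that its Methods do not call primary

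*Protocol article*

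**What the plan says.** The abstract (Methods/design) states: "The primary outcome will be the rate of symptom (fever, fatigue and coughing) recovery". It attaches no time point to that rate.

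The Methods (Outcomes and measurements) state: "The primary outcome will be the proportion of negative SARS-CoV-2 nucleic acid results on the 14th day". Symptom recovery appears there only among the secondary outcomes, and as a time: "The secondary outcomes will be the time to symptom recovery, the proportion of cases with reversion on chest CT". The rate of symptom recovery is not in the Methods list.

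The Sample size section takes its planning rates from an earlier trial of traditional Chinese medicine: "The rate of recovery of clinical symptoms was 91.2% in patients who received TCM treatment and 61.1% in patients who received conventional treatments". With 90% power, a 10% significance level and 10% loss, it arrives at 150 or more per group. It gives no rate for nucleic acid negativity.

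The Statistical analysis section sets two-sided tests at P < 0.05 and assigns tests by type of variable. It does not tie a test to a primary outcome. No section declares co-primary outcomes or a testing order.

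Study design and settings adds: "The study is designed as a randomized, placebo-controlled, multicentre trial". Randomization and blinding calls the trial open-label, and the Discussion lists the lack of a double-blind, placebo-controlled design as a limitation.

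**The concern.** Symptom recovery and virological clearance are different endpoints, and a treatment can affect one without the other. A reader of this article cannot tell which comparison decides whether the trial succeeded.

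Three things are at stake:

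- **Error control.** If the choice stayed open until results were known, success could be claimed on whichever outcome came out favourably, and 5% would no longer describe the risk of a false claim.
- **Power.** The stated power belongs to the abstract's outcome and says nothing about the Methods' outcome.
- **Bias.** Without a placebo, knowledge of treatment can influence reports of fatigue and cough more readily than a nucleic acid result. The two candidates therefore differ in their exposure to bias, and describing the trial as placebo-controlled hides that difference.

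**Working it through.** **1. The statements side by side**

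| Section | Outcome | Role | Time point |
|---|---|---|---|
| Abstract | Rate of symptom recovery | Primary | None |
| Sample size | Rate of symptom recovery | Basis for N | None |
| Outcomes and measurements | Nucleic acid negativity | Primary | Day 14 |
| Outcomes and measurements | Time to symptom recovery | Secondary | Visits to day 14 |

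**2. The plan's own figure (Sample size section)**

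Inputs: p1 = 0.912, p2 = 0.611, difference 0.301, power 90% (z = 1.2816), significance level 10%, loss 10%. The section does not state sidedness; two-sided is used first (z = 1.6449).

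n per arm = [z_α √(2p̄(1−p̄)) + z_β √(p1(1−p1) + p2(1−p2))]² / (p1−p2)², with p̄ = 0.7615.

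- √(2 × 0.7615 × 0.2385) = 0.6027
- √(0.0803 + 0.2377) = 0.5639
- n = (1.6449 × 0.6027 + 1.2816 × 0.5639)² / 0.0906 = 32.4, rounded up to 33
- After loss: 33/0.9 = 36.7, rounded up to 37

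At two-sided 5% the same formula gives 41, or 46 after loss. Across one- and two-sided tests at 5% and 10%, with pooled, continuity-corrected, unpooled and arcsine methods, the result after loss lies between 27 and 53 per arm. The stated 150 is not reproduced. That is a separate matter, but it means that N cannot be traced to either candidate outcome.

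**3. Power at the planned size**

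Evaluable per arm: 150 × 0.9 = 135. Two-sided α = 0.05, from the Statistical analysis section.

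Power = Φ{[d − 1.96 √(2p̄(1−p̄)/n)] / √[(p1(1−p1) + p2(1−p2))/n]}, where d = p1 − p2.

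For the quoted symptom rates: (0.301 − 1.96 × 0.05187)/0.04853 = 4.11, so power is 0.99998.

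The article gives no rates for day-14 negativity, so the control rates below are assumptions. Worked example, 80% v 90%: (0.10 − 1.96 × 0.04346)/0.04303 = 0.344, so power is 0.635.

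| Assumed control v treated | Power at 135 per arm | N per arm for 90% power, with 10% loss |
|---|---|---|
| 50% v 60% | 0.378 | 577 |
| 60% v 70% | 0.406 | 530 |
| 70% v 80% | 0.475 | 436 |
| 80% v 90% | 0.635 | 296 |
| 85% v 95% | 0.785 | 209 |

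Larger assumed differences do better: 70% v 85% gives 0.843 and 75% v 90% gives 0.905. The difference detectable with 90% power is about 19 points at a control rate of 50%, 16 at 70%, 13 at 80% and 9 at 90%.

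**4. False-positive risk if either outcome may be claimed**

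For two independent tests at 5%: 1 − 0.95² = 0.0975.

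**The case against.** The strongest reply is that a journal article condenses a fuller protocol. Version 1.0 of 1 February 2020 and the registration of 15 February 2020 are not shown, and both may name one primary outcome. This stands against one tempting inference: that the trial has no prespecified primary test at all, or that its primary was switched. The article shows only that it contradicts itself. The reply does not remove the contradiction, because two incompatible statements are a different thing from detail left to another document.

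Three further objections also limit the claim:

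- **Power.** A reader might infer that the trial is underpowered for day-14 negativity. The rates are assumed and the results span 38% to over 90%, so they show that power is unknown, not that it is low.
- **Error rate.** The 9.75% applies only if both outcomes are tested, the tests are independent and either may be claimed. No section plans that. Positive correlation between the tests would lower the figure.
- **Bias.** A reader might call the symptom outcome patient-reported. The article does not say who assesses it. It includes fever, and vital signs are recorded at every visit. The open-label argument applies mainly to fatigue and cough.

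Finally, it is tempting to recommend day-14 negativity because it is the more objective. But the abstract and the sample size both point to symptoms, recruitment began in February 2020 without blinding of treatment, and the article appeared in July 2021. Choosing on merit at that stage could itself be outcome switching. This objection is sound and shapes the fix.

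**Conclusion.** The point holds as an internal contradiction that must be corrected. Two sections point to symptom recovery and one to day-14 negativity, in current text, and nothing reconciles them. The 90% power statement cannot be carried over to the Methods' primary outcome, and the article offers no rate from which to replace it.

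The contradiction and the mismatch with the sample size rest on the text alone. The power range rests on assumed negativity rates, a 10-point difference, 10% loss and a normal approximation. The error-rate figure is conditional on a use of the two outcomes that the article does not announce.

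**What to change.** 1. Name one primary outcome, with its time point, in the same words in the abstract, Sample size and Outcomes sections. Take the one specified in protocol version 1.0 and the original registration. If those two differ, or leave the time point open, say so.
2. Disclose any change from those sources with its date, its reason and whether comparative data had been seen.
3. List the other outcome as secondary.
4. Restate the power or the detectable difference for the chosen primary at N = 300 and two-sided 0.05, the level used in the analysis, and give the source of the assumed rates.
5. Correct the placebo-controlled wording in Study design and settings to match the open-label design.

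The cost is a documented amendment and changed wording in four sections, with no new procedures. If day-14 negativity is the primary, the restated figure may be much less favourable than the present claim. That figure should be accepted openly at N = 300, as a larger detectable difference, rather than met by enrolling more patients.

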### Plan for retaining participants

Methods are needed to promote participant retention. First, we will select the coordinator and nurse carefully and train them strictly before the trial begins. Furthermore, we will focus on daily communication and monitoring. The coordinator and nurse should have empathy and good communication skills to gain the patient’s trust to improve patient retention and completion of the follow-up period. In addition, we will provide extra incentives.

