### Statistical analysis

We will not conduct subgroup or adjusted analyses of the trial. The independent statistical analysts will be responsible for the data analysis. All patients will be analysed on the basis of intent-to-treat analysis, including all randomized subjects who take Baidu Jieduan granules at least once and have follow-up information recorded. In the case of missing data, multiple imputation will be carried out to generate missing values. A per-protocol analysis, which includes patients who completed the trial without conflict with the major protocol, can be conducted as appropriate. Then, the statistician will submit statistical reports in a timely manner to the study director. The statistical analysis will be performed in a blinded manner using SPSS 20.0 software. Continuous variables characterizing each study group will be expressed as the mean with standard deviation or median with interquartile range. Categorical variables will be reported as frequencies and proportions. Continuous outcomes will be analysed by unpaired Student’s *t*-test or Wilcoxon’s nonparametric statistic, while count data will be compared using a chi-square test or Fisher’s exact test. All statistical tests will be two-sided. *P* < 0.05 will be considered statistically significant. We will not carry out an interim analysis.

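### Time to symptom recovery is evaluated only on days 3, 5, 7 and 14, so unless recovery dates are recorded separately a second-week recovery is known only to lie between days 7 and 14

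*Protocol article*

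**What the plan says.** In the protocol article, Outcomes and measurements lists a time outcome for symptoms: "The secondary outcomes will be the time to symptom recovery". It defines the event but gives no rule for dating it: "Symptom recovery is defined as the complete disappearance of fever, fatigue and coughing symptoms". It then fixes when the primary and secondary outcomes are evaluated, which "will occur at five points (before treatment and the 3rd, 5th, 7th and 14th days of hospitalization").

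The Methods/design part of the abstract gives the same day numbers, counted from a different origin: "The outcomes will be assessed at baseline and at 3, 5, 7 and 14 days after treatment initiation". Interventions sets the treatment period: "The Baidu Jieduan granules will be administered orally two times a day for 14 days". Statistical analysis says: "Continuous outcomes will be analysed by unpaired Student’s *t*-test or Wilcoxon’s nonparametric statistic".

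The article mentions no symptom diary, daily symptom record or recalled recovery date. Daily contact appears only under Plan for retaining participants: "Furthermore, we will focus on daily communication and monitoring". Telephone follow-up after discharge appears under Quality control and is not tied to outcome dating.

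**The concern.** A time outcome is only as fine as the schedule on which the event can be seen. Here the widest gap between evaluations covers the whole second half of the 14-day treatment period. A patient whose symptoms clear on day 8 and one whose symptoms clear on day 14 look the same at the visits.

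This does not depend on the choice of test or on where the clock starts. A survival method with a well-defined origin would still see only four post-baseline days. Nor can a later analysis plan recover dates that were never collected.

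What is at stake is the size of the reported recovery times and of the difference between arms, because both would partly reflect the visit days. A t-test would also treat a value of 14 as exact when it stands for a 7-day interval.

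**Working it through.** The plan gives no expected recovery time, so there is no figure of its own to reproduce.

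**1. The schedule alone (no assumption about recovery times).** Evaluation days are 0, 3, 5, 7 and 14, so the gaps are 3, 2, 2 and 7 days. A recovery on any of days 8 to 14 is first seen on day 14, up to 14 − 8 = 6 whole days late if dated by that visit. An arm's median can only be 3, 5, 7, 14 or not reached. Any true median above 7 and up to 14 reads as 14, so 8 v 10 days and 9 v 11 days both read as 14 v 14.

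**2. Illustration from the planning rates.**

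Inputs: recovery rates of 61.1% (conventional) and 91.2% (TCM), from Sample size. Assumptions, because the article states neither: these are day-14 rates, and recovery is exponential.

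| Quantity | Control | Granules |
|---|---|---|
| Daily hazard h = −ln(1 − rate)/14 | −ln(0.389)/14 = 0.0674 | −ln(0.088)/14 = 0.1736 |
| True median, ln 2/h | 10.3 days | 4.0 days |
| Recovered by day 3 / 5 / 7 / 14, 1 − exp(−h × day) | 18 / 29 / 38 / 61% | 41 / 58 / 70 / 91% |
| Share of recoveries after day 7, (F14 − F7)/F14 | (61.1 − 37.6)/61.1 = 38% | (91.2 − 70.3)/91.2 = 23% |
| Mean lateness if dated day 14 | 3.8 days | 4.2 days |
| Median as read at the visits (first day with at least 50% recovered) | 14 | 5 |

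F7 and F14 are the percentages recovered by days 7 and 14. Mean lateness is 7 − [1/h − 7q/(1 − q)] with q = exp(−7h):

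- Control: q = 0.624, giving 3.8 days.
- Granules: q = 0.297, giving 4.2 days.

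The true difference in medians is 10.3 − 4.0 = 6.3 days. Read at the visits it is 14 − 5 = 9 days, an overstatement of 2.7 days. Step 1 shows that the error can also run the other way and hide a 2-day difference.

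**3. Power.** Simulations used 135 evaluable per arm (150 less 10% loss), two-sided 0.05, and compared recovery read daily with recovery read on the four days.

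- Planning-rate scenario: 100% power on both readings.
- Smaller assumed effects, rank test: a loss of about 0 points for exponential times with medians 10.3 v 7.2, 3 to 5 points for Weibull shape 2 with medians 10 v 8.5, and 9 to 11 points for Weibull shape 3 with medians 10 v 9.
- Two-day differences in medians, Weibull shapes 1.5 and 2.5, rank test: a loss of 0 to about 3 points.

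None of the smaller effects or shapes is in the article.

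**The case against.** The strongest reply is that the article fixes when outcomes are evaluated, not how a recovery is dated. An evaluator on day 14 could take the date from the ward chart or ask the patient. The article is a condensed account, and its study-procedures figure, the full protocol and the case report form are not shown; any of them might hold a daily record. This stands, and it makes the point conditional. A reader might infer that every second-week recovery will be dated day 14, or that the outcome cannot be measured in that week. The article does not support either: it states no dating rule, and even on the visit days alone the interval (7, 14] is known.

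A reader might also infer that sites will hold daily symptom data and discard them. Daily communication is described as a retention measure. It suggests that a daily record is feasible, not that one exists.

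A third tempting reading is that the trial loses power. At the planning rates it loses none, and the larger losses need assumptions from outside the article.

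Finally, the schedule is the same in both arms, so it does not by itself create a difference where there is none, and a sparse visit schedule is a common trade-off in an emergency inpatient trial. That limits the harm to the precision of estimated times. It does not remove it, since the schedule is stated outright and no part of the article shown fills the gap.

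**Conclusion.** The point holds in a limited form. Followed as written, and unless a recovery date is recorded separately, the schedule places a second-week recovery only in (7, 14] and restricts a reported median to 3, 5, 7, 14 or not reached. That much rests on the stated days alone.

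The size rests on two assumptions, that the planning rates apply at day 14 and that recovery is exponential. On these, roughly two in five control recoveries and just under one in four granule recoveries are affected, and the difference in medians reads 9 days in place of 6.3.

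The harm is to the estimated times and their difference. Loss of power is not a reason for the change. Proportions read on day 14 are unaffected, including the nucleic acid proportion that Outcomes and measurements names as primary. Time to a negative nucleic acid result has the same gap, but there each reading needs a sample.

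**What to change.** 1. Record fever, fatigue and cough as present or absent once a day to day 14: from the ward chart in hospital, and by the existing telephone follow-up or a diary after discharge.
2. Date recovery as the first day on which all three are absent and remain absent for a prespecified period or through day 14. Without a sustained-absence rule, daily reading gives more chances to count a transient remission as recovery.
3. Keep the four visit days for assessments that need a procedure. State that time to negative nucleic acid is interval-censored between sampling days, and analyse it so.
4. If the full protocol already has a daily record or a dating rule, say so in Outcomes and measurements; steps 1 and 2 then need only a sentence.

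Cost: one three-item daily line on the case report form, with no added visit or procedure. The downsides are a little more data entry and more self-reported assessments by patients who know their allocation.

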### Safety outcomes

All safety-related indexes, including vital signs, complete routine blood indexes, routine general urine indexes, biochemical indexes, faecal occult blood test results and electrocardiogram results, will be tested and recorded in the CRF at every visit. The biochemical test includes C-reactive protein, hepatic function indicators (alanine transaminase, aspartate transaminase, alkaline phosphatase, total bilirubin and gamma-glutamyltransferase) and renal function indicators (blood urea nitrogen and serum creatinine). Any AE will be evaluated by a professional researcher at each visit and recorded on the CRF.

### Adverse event (AE) reporting

An AE is defined as any undesirable syndrome connected with the administration of Baidu Jieduan granules in a patient [16]. Any AE needs to be recorded in the form immediately and then evaluated by the physician and the corresponding coordinator. All related information, including the occurrence time, severity, duration, measures adopted and outcome, can be reported to the sponsors, ethics committees and drug regulatory authorities in accordance with the provisions. We will follow all subjects with AEs.

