Baidu Jieduan granules evolved from the classical TCM prescription Maxing Shigan decoction and our experiential prescription, Jinhong decoction. Our previous studies have demonstrated that Jinhong decoction, composed of *Rheum palmatum L.* stem, *Sargentodoxa cuneata* and *Taraxacum mongolicum*, can inhibit the levels of TNF-α, IL-6, IL-8 and other inflammatory cytokines; protect against excessive inflammatory responses; and maintain an organism’s balance between inflammation and anti-inflammatory responses in infectious diseases [11, 12]. Recent research has shown that Maxing Shigan decoction is regarded as an antipyretic, anti-inflammatory, antiviral, antitussive and antiasthmatic agent and can be used to treat COVID-19 [13]. Therefore, Baidu Jieduan granules should have beneficial and curative effects on COVID-19. However, there is insufficient evidence to show the clinical efficacy of Baidu Jieduan granules. Hence, we aim to conduct a multicentre, randomized trial to evaluate the efficacy and safety of Baidu Jieduan granules in the treatment of COVID-19. Furthermore, this trial can serve as a reference for TCM in the prevention and treatment of COVID-19 worldwide.

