### Randomization and blinding

The enrolled participants will be randomly assigned to the Baidu Jieduan granule group or the conventional treatment group according to random codes. The random sequence of 300 participants from 4 medical centres will be generated by SPSS 19.0 and stratified by centre. Two sets of random codes will be stored in opaque envelopes, which will be sent to the research sponsor and each of the centres. Thereafter, the drug administrators will arrange the nurse to dispense the study drug in the order of random numbers. This will be an open-label study. The statistical analysis will be carried out by the Professors of Statistics of Shanghai University of Traditional Chinese Medicine, who will be blinded to the patient allocation.

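### The adverse event definition requires a connection with the granules, so control-arm events fall outside it and recorded AE incidence cannot be validly compared between arms

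*Protocol article*

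**What the plan says.** The Introduction makes safety an aim of the randomized trial: "we aim to conduct a multicentre, randomized trial to evaluate the efficacy and safety of Baidu Jieduan granules". Under Interventions, the arms differ only in the granules: "The participants will be categorized into two groups receiving either standard Western medicine alone", or "the combination of Baidu Jieduan granules two times a day for 14 days plus standard care". Under Randomization and blinding: "This will be an open-label study".

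The only definition of an AE is in the section on AE reporting: "An AE is defined as any undesirable syndrome connected with the administration of Baidu Jieduan granules in a patient". The same section has each AE recorded at once and then assessed by a physician and a coordinator.

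Safety outcomes contains two separate requirements. A panel of vital signs, blood, urine, biochemistry, faecal occult blood and ECG "will be tested and recorded in the CRF at every visit". Then, for events: "Any AE will be evaluated by a professional researcher at each visit and recorded on the CRF". The Abstract says that AEs are monitored for the whole trial. Neither section names an arm. The Ethics section speaks of AEs attributable to the study, which is wider than events connected with the granules.

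**The concern.** A randomized control group shows how many untoward events occur from COVID-19 and standard care alone, so that an excess in the treated arm can be read as an effect of the treatment. That works only if events are counted by the same rule in both arms.

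The stated definition makes relatedness to the granules a condition of being an AE. It describes a suspected reaction to the granules rather than an adverse event. Two things follow:

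- A control patient with vomiting, rash or loose stools has no AE under the definition, while a granule patient with the same complaint may have one.
- In the granule arm, what enters the record depends on an attribution judgement made with treatment known. A harm put down to COVID-19 or to standard care drops out of the AE record.

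The two effects bias the comparison in opposite directions. The first can create an apparent excess where none exists; the second can hide part of a real one. The analysis cannot undo either, because events that were not recorded as AEs during the trial are hard to recover afterwards.

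**Working it through.** **Step 1: the text.** The protocol article states no AE rate, so there is no figure to reproduce. The check is whether a control-arm event can meet the definition.

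| Place in the article | What it fixes | Can a control event count as an AE? |
|---|---|---|
| AE reporting | An AE is connected with administration of the granules | No |
| Interventions | Control arm has standard Western medicine alone | No granules are administered, so no connection is possible |
| Safety outcomes, last sentence | Any AE is evaluated and put on the CRF | Uses the defined term, so no |
| Abstract, Methods/design | AEs monitored throughout | Uses the defined term, so no |
| Ethics | AEs attributable to the study | Possibly, but this does not redefine the term |
| Safety outcomes, test panel | Tests at every visit | Does not depend on the AE definition |

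The result is the same whether connected is read as caused by the granules or merely as following a dose. Study design and settings calls the trial placebo-controlled, which conflicts with the Interventions and Discussion sections. Even a placebo would not help here, because placebo patients would not receive granules.

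**Step 2: how few events would mislead.** Inputs from the article: 150 per arm (Sample size); two-sided tests at P < 0.05, with Fisher's exact test available for counts (Statistical analysis). Input from Step 1: 0 recordable AEs in the control arm.

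With x granule patients recorded and 0 controls, and equal arms, the two-sided Fisher p is

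p = 2 × C(150, x) / C(300, x)

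- x = 5: p = 2 × (150·149·148·147·146) / (300·299·298·297·296) = 2 × 0.0302 = 0.060
- x = 6: p = 2 × 0.0302 × 145/295 = 2 × 0.0148 = 0.030

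Six patients, or 6/150 = 4%, are enough.

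**Step 3: chance of a spurious excess when true rates are equal.** Assumptions, none of them from the documents: a fraction r of patients in each arm has an untoward event, and a share s of those in the granule arm is judged connected. The number recorded in the granule arm is then binomial with n = 150 and q = r × s, and the chance of a significant result is P(X ≥ 6).

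| q | Combinations of r and s giving it | Expected recorded, 150 × q | P(X ≥ 6) |
|---|---|---|---|
| 1.25% | 5% × 0.25 | 1.875 | 0.012 |
| 2.5% | 5% × 0.5; 10% × 0.25 | 3.75 | 0.175 |
| 5% | 5% × 1; 10% × 0.5; 20% × 0.25 | 7.5 | 0.766 |
| 7.5% | 30% × 0.25 | 11.25 | 0.972 |
| 10% | 10% × 1; 20% × 0.5 | 15 | 0.998 |

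The outcome depends almost wholly on how readily staff attribute events to the granules. At low q the artefact is negligible as a test result, but the two counts still measure different things.

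**The case against.** The strongest reply is that the definition is loose wording and would not be followed literally. The Abstract and Safety outcomes provide for AE monitoring and recording without naming an arm, and Ethics uses a wider phrase, so staff could reasonably record control-arm events. A zero in the control arm is therefore a consequence of the text, not an established fact about practice. This stands as a caution on the illustration. It does not rescue the definition: if sites mean to record control events, the definition is wrong, and if they follow it, the comparison is lost.

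A second reply is that the AE section puts recording before evaluation, so no investigator rules on causality first. This softens the point but does not remove it, since deciding that something is an AE at all already requires a connection with the granules.

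A third is that detail may sit in a fuller protocol or SAP. But the concern is a stated rule, not missing detail, and an analysis plan cannot tabulate events that were never recorded as AEs.

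A reader might also infer three stronger things, which the document does not support:

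- *That safety cannot be compared between arms at all.* The test panel in Safety outcomes is recorded at every visit with no arm restriction stated, and it stays comparable.
- *That harms judged unrelated are never captured.* Those that show in laboratory tests, vital signs or ECG are captured whatever their attribution. The loss concerns events, mainly symptomatic ones, that these tests do not show.
- *That an excess of events resembling COVID-19 would be invisible.* Outcomes and measurements separately counts patients regrouped as severe and follows recovery from fever, fatigue and coughing, so such an excess could partly appear there.

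**Conclusion.** The point holds for recorded AE incidence and no further. As worded, control-arm events lie outside the AE definition, and open-label attribution decides what enters the record in the granule arm. A table of AEs by arm would not be a valid comparison, in a trial that sets out to "evaluate the efficacy and safety of Baidu Jieduan granules in the treatment of COVID-19". The panel of safety tests and the severe-disease outcome remain comparable, and the primary outcome is not touched.

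The size is illustrative. If the definition is applied literally and the control count is 0 of 150, 6 recorded patients in the granule arm give p of about 0.03. Under equal true rates, the chance of such a result runs from about 1% to over 99% as the proportion of granule patients with an event judged connected rises from 1.25% to 10%. These proportions are assumptions. The conclusion that the counts are not comparable follows from the text and does not depend on them.

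**What to change.** - In the section on AE reporting, define an AE as any untoward medical occurrence after randomization, in either arm, regardless of cause.
- Record relatedness to the granules as a separate CRF field, completed after the event has been entered.
- Tabulate all AEs by arm, with related AEs as a further table.
- Align the AE wording in the Abstract, Safety outcomes, AE reporting and Ethics so that all four use the one definition.

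The cost is the wording of the definition and CRF guidance, plus slightly more event recording in the control arm. The visits are already planned, and neither sample size nor the efficacy analysis changes. Any control-arm events from before the change may be under-recorded, and the report should say so.
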